### Study sample size and duration

We performed a sample size calculation for survival endpoints based on the recommendation of Dupont and Plummer [13]. We have set the alpha error at 0.05 and the beta error at 0.2 and assumed a median survival time in the control group of 15 years. We specified a hazard ratio of the control group relative to the experimental group of 1.2, an accrual time during which patients are recruited of ten years and no additional follow-up time after end of recruitment. Since we are interested in various endpoints we chose an extreme ratio of control to experimental patients of 5 to be on the safe side. Based on these assumptions the required sample size is 1545. Given the size of the catchment's area we anticipate to include about two hundred new patients annually which lead to a sufficient number of patients to perform analyses after the end of the recruitment period.

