### Statistical analysis

Epidemiologic data and patients' descriptives available on continuous scales will be presented with medians, interquartile ranges or means and standard deviations as appropriate. Categorical data will be presented as rates and percentages.

Association of individual (independent) variables on the outcome variables will be reported using correlation coefficients. Results from univariate analysis will inform multivariate modeling.

Assessment of causal associations will be performed using multivariate models including potential confounders along with the independent variables of interest. Prognostic scores will be built using either multivariate logistic regression analysis or Cox proportional hazard models. Models will be validated in cross samples. Calibration and discrimination of the cross-validated prognostic instruments will be assessed using the Brier Score.

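### The Brier score is named as the measure of both calibration and discrimination of the prognostic scores, but one Brier value mixes the two and cannot show which is good or bad

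*Protocol article*

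**What the plan says.** The Statistical analysis section of the protocol article sets out prognostic modelling in three steps.

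- Model: "Prognostic scores will be built using either multivariate logistic regression analysis or Cox proportional hazard models".
- Validation: "Models will be validated in cross samples".
- Performance: "Calibration and discrimination of the cross-validated prognostic instruments will be assessed using the Brier Score".

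The article names no C-index, AUC, calibration slope, calibration plot or decomposition of the Brier score. It gives no prediction horizon and does not say whether the score would be weighted for censoring.

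On follow-up, the Study sample size and duration section assumes "an accrual time during which patients are recruited of ten years and no additional follow-up time after end of recruitment" and expects "a sufficient number of patients to perform analyses after the end of the recruitment period". The Abstract gives the study a minimum length of ten years with no upper limit. The Procedure section schedules visits at 3, 6 and 12 months after treatment and yearly from then on.

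**The concern.** The performance sentence names two properties and gives one number for both. Discrimination is whether the score ranks men correctly. Calibration is whether the predicted risks are right. The Brier score is an overall squared prediction error. It falls as discrimination improves, rises with miscalibration, and has a level set by how common the outcome is. A reader given only the value cannot tell which of these produced it.

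The distinction affects what is done next. A score that ranks well but is miscalibrated can be recalibrated, whereas one that does not rank should be dropped. The Objectives include assessing biomarkers, where ranking matters, and individualised treatment recommendations. To the extent that prognostic scores feed those recommendations, correct absolute risks matter too.

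**Working it through.** **1. The plan's own figures.** The Statistical analysis section states no figure. The follow-up inputs come from the sample size section, and they can be confirmed by reproducing its 1545. Take exponential survival, medians of 15 and 15 × 1.2 = 18 years (average 16.5), uniform accrual over 10 years, no further follow-up, two-sided alpha 0.05 and power 0.8.

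- Death probability by analysis: p = 1 − (1 − e^(−10λ))/(10λ), with λ = ln 2/16.5. This gives p = 0.1835.
- n = (1.960 + 0.842)² / (ln 1.2)² × (1 + 1/5) / 0.1835 = 1544.3, rounded up to 1545.

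The match confirms ten years of accrual and no added follow-up as the planning inputs. (The formula yields the size of the experimental group; that is a separate matter.) The same expression gives 0.199 at a median of 15 years and 0.170 at 18 years. Weighted 5:1 this is (5 × 0.199 + 0.170)/6 = 0.194, so an event risk of 0.19 is a fair illustration.

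**2. Same Brier score, different models.** Simulation of 2,000,000 men with log-odds of risk a + z, z standard normal, and a = −1.72 so that mean risk is 0.19. The SD of 1 is an assumption. The Brier score splits as uncertainty − resolution + reliability:

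- Uncertainty = 0.19 × 0.81 = 0.1539 for every model.
- Resolution rewards separation of risks. For the full ranking it is 0.1539 − 0.1338 = 0.0201.
- Reliability is the penalty for miscalibration.

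| Model | AUC | Calibration | Uncertainty − resolution + reliability | Brier |
|---|---|---|---|---|
| A. Constant 0.19 | 0.50 | mean correct | 0.1539 − 0 + 0 | 0.154 |
| B. True risks | 0.745 | perfect | 0.1539 − 0.0201 + 0 | 0.134 |
| C. Coefficient of z doubled, mean held at 0.19 | 0.745 | slope 0.5 | 0.1539 − 0.0201 + 0.0087 | 0.142 |
| D. Weaker model (log-odds SD 0.72, found by matching C's Brier score) | 0.69 | perfect | 0.1539 − 0.0114 + 0 | 0.142 |
| E. Coefficient of z doubled, intercept unchanged | 0.745 | slope 0.5, mean prediction 0.257 | 0.1539 − 0.0201 + 0.0205 | 0.154 |
| F. Whole linear predictor doubled | 0.745 | slope 0.5, mean also wrong | 0.1539 − 0.0201 + 0.0113 | 0.145 |

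C and D tie: one ranks better and is badly calibrated, the other ranks worse and is perfectly calibrated. A and E also tie. B, C, E and F rank men identically, yet their scores run from 0.134 to 0.154.

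A second simulation (400,000 men, 5-year risk 0.206) gave a further tie at 0.164. It was between a constant calibrated prediction and a model with AUC 0.74 whose mean prediction was 0.344 against 0.206 observed.

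**3. Censoring.** Assume uniform entry over 10 years, analysis at the end of recruitment, and "assumed a median survival time in the control group of 15 years" with exponential survival, so λ = ln 2/15 = 0.0462. Potential follow-up is then uniform on 0 to 10 years, and 5/10 = 50% of men have under 5 years. The share with unknown vital status at horizon t is (1 − e^(−λt))/(10λ):

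- 1 year: 0.0452/0.462 = 9.8%
- 5 years: 0.2063/0.462 = 44.6%
- 10 years: 0.3700/0.462 = 80.1%

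In the second simulation the 5-year Brier score of a well-calibrated model came out as follows:

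- 0.141 with complete data
- 0.176 with men of unknown status dropped
- 0.123 with them counted as alive
- 0.141 with inverse-probability-of-censoring weights

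The two naive errors (+0.035 and −0.018) are about as large as, or larger than, the roughly 0.02 gap between a useless and a good model.

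**The case against.** **Other measures are not excluded, and an article condenses.** Decomposition, plots, horizons and censoring weights are commonly left to a fuller document, and the Brier score has a recognised split into reliability and resolution. This holds for the details. It does not rescue the sentence, which states a choice of measure for two named properties and mentions no split.

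**A badly overfitted score need not look useless.** A reader might infer that any score with calibration slope 0.5 would tie with a no-information model. The calculation does not support that. With the mean preserved (C) the score is 0.142, and with the whole predictor doubled (F) it is 0.145; both are below 0.154. The tie at 0.154 requires the mean prediction to be too high as well, 0.257 against 0.19. A slope of 0.5 is also an extreme case. What survives is the C and D tie, and the general fact that the value does not identify its components.

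**The Brier score is usable here.** A reader might also infer from the short follow-up that it cannot be computed. The article does not say that. It fixes neither a horizon nor an unweighted score. Logistic scores for outcomes at 3 to 12 months would be little affected. Even at 5 years about 1,000 of some 2,000 men ("we anticipate to include about two hundred new patients annually" for ten years) would have been enrolled early enough. The absence of added follow-up is a sample-size input, and the Abstract allows a longer study. This objection stands, so censoring is only a caveat for long-horizon Cox scores.

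**Nothing is lost in the data.** This also stands. The right measures can be produced at analysis from the same models, so it would go too far to say the study could never tell which instrument is usable.

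**Conclusion.** The point holds as a defect in a stated rule. The sentence assigns calibration and discrimination to a measure that, as a single value, reports neither separately. Under event risk 0.19 and log-odds SD 1, a difference in AUC of 0.745 against about 0.69 is exactly offset by a calibration slope of 0.5 against 1, with both models at about 0.142. The sizes depend on those two inputs, the second of which is assumed; the principle does not.

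Censoring is secondary. It applies to Cox scores at long horizons, and the figures of 50% and 44.6% at 5 years rest on uniform accrual, analysis directly after recruitment and exponential survival with a 15-year median. The documents do not support saying that the Brier score cannot be computed.

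**What to change.** Replace the performance sentence with:

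> Discrimination will be assessed by the C-index or (time-dependent) AUC, calibration by calibration intercept, slope and plot, and overall accuracy by the Brier score, all from held-out predictions; for Cox scores at a fixed horizon the Brier score will be weighted for censoring.

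This is a change of wording only. The added measures are standard output from the same fitted models and need no new data. The one downside is slightly more analysis output to report.

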## Discussion

This paper describes the rational, methodology and design of a prospective, multi-center cohort study within the Canton of Zurich including patients with localized prostate cancer independent of treatment finally chosen. We intend to set up a prospectively acquired clinical database including quality of life data and lifestyle factors with corresponding prostate tissue specimens (biopsy cores and/or whole organ, dependent of treatment finally chosen) and further bio-samples (blood and urine).

Based on the results we will identify treatment specific influences on quality of life and formulate appropriate treatment recommendations. Examination of biomarkers will contribute to a better understanding of the underlying biological mechanisms and will guide the development of new diagnostic and prognostic algorithms. Therefore this study will help to improve decision-making. It will help patients weighing the pros and cons of various treatment modalities and it will help physicians to inform their patients adequately.
